## Abstract

**Aim:**

To determine whether the number of residents' preferences and needs together with the actions taken to satisfy them recorded into their ‘life‐and‐care plans’ will increase and the process of shared decision‐making will improve the residents' psychosocial well‐being.

**Background:**

Shared decision‐making is defined as a process where healthcare professionals and patients make decisions together, using the best available evidence.

The aims of the present study were to assess the feasibility and acceptability of an SDM framework for care planning in long‐term care facilities and its potential effectiveness on the proportion of dementia residents whose own preferences and needs and the related actions, are known, satisfied and documented in their ‘life‐and‐care plans’.

**Design:**

The current project is a feasibility trial and it was approved in November 2013.

**Methods:**

Research subjects are triads composed of the resident with dementia, a family caregiver and the professional usually taking care for the resident. Professional caregivers of two nursing homes, one located in Italy and one in the Netherlands, will receive a specific training in SDM principles and will guide the SDM interview in the triad. The primary outcome will be the proportion of residents whose preferences and needs, together with the related actions to meet them, are known, documented and satisfied in their ‘life‐and‐care plans’.

**Trial registration:**

NCT02118701.

## Introduction

Long‐term care (LTC) residents with dementia have complex needs and can have difficulties in articulating them, since the ability to express their wishes is impaired (Hancock *et al*. 2006). This does not mean that they do not have their own preferences, that they are completely unable to articulate preferences and feelings (Carpenter *et al*. 2007), or that they are unable to answer simple questions about needs and preferences (Whitlatch 2010). While the abilities to answer fact‐based questions deteriorate after the early stages of dementia, the abilities to answer preference questions remain more stable over time (Whitlatch 2010). Some studies have shown that it is possible to assess individuals with dementia's personal preferences and to enhance their decision‐making involvement (Whitlatch 2010). Such studies have shown a positive link between the involvement of people suffering from dementia in decision‐making and their quality of life (Fetherstonhaugh *et al*. 2013).

## Background

Shared decision‐making (SDM) is defined as a process where the healthcare professional and the patient make decisions together, using the best available evidence (Charles *et al*. 1997, 1999, Elwyn *et al*. 2010). It requires sharing of information and agreement by both parties on the decisions taken (Elwyn *et al*. 1999). The SDM process entails the patient's and family's expression of their preferences and their discussion with the healthcare professional, who on his side elicits the patient's thoughts about pro and cons of the available treatments or options, aiming to reach agreement about healthcare decisions to be made (Elwyn *et al*. 2001). SDM is a component of a person‐centred care approach, a recognized theoretical framework that can guide the provision of high quality dementia care. Its aim was to acknowledge the identity and personhood of people with dementia. According to Edvardsson's review, the two key elements of a person‐centred care approach for people with severe Alzheimer disease are to take into account the person with dementia's point of view and to offer SDM (Edvardsson *et al*. 2008).

Reciprocity, by the contribution of the patient in the decision‐making process, is an important element that can improve health and well‐being in frail older people and that indirectly has an impact on the effectiveness of psychosocial interventions (Vernooij‐Dassen *et al*. 2001). Moreover, SDM seems to be the most typical pattern that occurs in decision‐making situations where the person with dementia, a family member and a professional caregiver are involved (Smebye *et al*. 2012). Despite this potential, SDM is not often used in LTC settings with persons with dementia or even with their family caregivers, whose views are frequently not included and documented in care planning (Cohen 1991, Broderick & Coffey 2013).

### Context

The study runs within the IMPACT project (Implementation of quality indicators in Palliative Care study) funded by the EU 7^th^ Framework Programme that involves five European countries, among which the Netherlands and Italy. Life‐and‐care plans, as tools for goal planning and for care and registration of treatment actions, are compulsory in both Dutch and Italian LTC facilities. In these settings, a multidisciplinary team assesses residents during the first two weeks following admission. When assessment is completed, a ‘life‐and‐care plan’ is developed and compulsorily signed by the professional responsible for the plan, the family caregiver and if possible the resident. In the Dutch LTC facility, usually a nurse is responsible for the plan and in the Italian setting, a nurse or any available and qualified member of the multidisciplinary team. The structure of the plans adopted in both countries is similar and consists of four main sections: Problems; Goals; Actions; Evaluation. Problem areas primarily cover: mental and physical well‐being; activities of daily living; and cognitive and social functioning. Plans are updated as changes in the resident's condition occur and at least once a year. The choice to develop and implement an SDM framework in care planning in the Netherlands and in Italy was primarily based on the existing collaboration between the University of Bologna and the University of Nijmegen. Second, SDM is an issue that is receiving growing attention in both countries. In the Netherlands, a policy called ‘family participation’ has been developed in the 1990s to promote the participation of family members in the care planning of their relatives admitted into nursing homes (Dijkstra 2007). However, a structured involvement of both family carers and dementia residents by using SDM in LTC settings has not become common practice. In Italy, the National Health Plan developed in 2011 underlines the importance of involving citizens and patients in the healthcare decision‐making process. However, there are only few studies on SDM carried out in this country and none of them was conducted in the dementia care area (Goss *et al*. 2011).

## Aim and objectives

This study has the following primary objectives: (1) to assess the feasibility and acceptability of an SDM framework in care planning to be used both to assess the preferences and (un)met needs of the LTC resident with dementia and his family caregiver and to plan tailored and shared actions based on the assessment outcomes; (2) to investigate how the process of SDM evolves between the resident, professional caregiver and family caregiver; (3) to investigate whether it is acceptable to professionals, residents and families becoming, embedded into the clinical practice of the involved LTC settings in Italy and the Netherlands.

The secondary objectives intend to explore the impact of the SDM framework on:
the dementia residents' quality of lifethe family carers' quality of life and sense of competencethe professional caregivers' job satisfactionthe caregivers' satisfaction with the SDM interventionthe organizational context where it takes place, i.e. barriers and facilitators, as perceived by the professionals.

In particular, we want to determine whether the SDM framework is likely to increase the number of residents' preferences and needs together with the actions taken to satisfy them recorded into their ‘life‐and‐care plans’ and whether it improves the residents' psychosocial well‐being.

## Design and methods

### Study design

The current project is a feasibility study. The research population consists of dementia residents living in the selected LTC settings, their main family carers and the professional caregivers usually taking care for the residents. The subjects are organized in triads: each triad is composed by the resident with dementia, the family and the professional caregiver. A multi‐method approach (Morse 2003) will be adopted to provide an in‐depth description of the SDM process developed in the triad. Quantitative data based on residents' personal files and on the screening and evaluation measures collected from professionals and family caregivers will be used.

### Subjects and settings

Two nursing home wards in the Netherlands and two nursing home wards in Italy are involved. In each country, one ward will randomly be assigned to the intervention group and the other to the control group. The same number of residents, family caregivers and healthcare professionals will be assessed in both groups and the same tools will be used. In the Netherlands two Dementia Special Care (DSC) units in the same nursing home will be recruited, whereas in Italy two different nursing homes will be enlisted, being similar in numbers of residents admitted, staffing patterns and level of medical and psychosocial care provided, as described in their charters of services. To avoid contamination, in the Netherlands the professionals working in the experimental DSC unit will not be the same as the ones working in the control DSC unit.

In each experimental and control nursing home ward, 20 dementia residents will be included, based on the following inclusion criteria: (1) having a diagnosis of dementia based on DSM IV (American Psychiatric Association 2000); (2) being able to give informed consent or, if legally incapable, having a family caregiver who can give informed consent for them; and (3) being supported by one primary family caregiver who agrees to participate and to be involved in the study too.

Inclusion criteria for the principal professional caregivers are: (1) being a member of the multidisciplinary team who is used to being directly involved in the care planning process; and (2) being a key staff member in the provision of residents' care and consequently to know the identified residents well. In both countries, at least eight healthcare professionals will be recruited to attend the training provided for the project and will later conduct the SDM interviews with 20 residents and their family caregivers.

Thus, the entire experimental group is composed by a total of 40 dementia residents, 40 family carers and about 16 healthcare professionals. These participants will be compared with the two other control nursing home wards that will be asked to involve the same number of subjects. After the selection is completed, a researcher will check the accuracy of the choices based on the requested inclusion criteria.

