## Data analysis

Quantitative data will be analyzed using the Statistical Package for Social Science (SPSS). The proportion of residents whose SDM documentation on needs satisfaction has been fulfilled, will be analyzed using the Fischer's exact test. Secondary outcomes, at the level of residents, professional and informal caregivers, will be calculated using parametric and non‐parametric tests, making comparison between and within groups. Descriptive statistics will be used to compare the experimental and control nursing home wards for socio‐demographic characteristics and baseline variables. In each country, the focus group discussions' content will be translated into English. Two independent researchers will code the data by using a constant comparative method (Johnson *et al*. 2012). Each researcher will develop and label categories with appropriate codes outlining the core concepts of the focus group interviews. Then, the codes will be combined in clusters to define the concepts and identify similarities and differences between the interviews (Boeije 2002). Codings will be discussed until consensus will be reached.

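### Residents appear to be chosen in wards already labelled experimental or control, and an eligibility check afterwards cannot prevent selection that differs by arm

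*Protocol article*

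**What the plan says.** The Subjects and settings section of the protocol article sets out the allocation and the selection of residents.

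- **Allocation:** "In each country, one ward will randomly be assigned to the intervention group and the other to the control group".
- **Inclusion:** "In each experimental and control nursing home ward, 20 dementia residents will be included, based on the following inclusion criteria". The criteria are a DSM-IV dementia diagnosis, consent by the resident or a family caregiver, and "being supported by one primary family caregiver who agrees to participate and to be involved in the study too". They set no limit on dementia severity or ability to communicate.
- **Control participants:** "These participants will be compared with the two other control nursing home wards that will be asked to involve the same number of subjects".
- **Check on selection:** "After the selection is completed, a researcher will check the accuracy of the choices based on the requested inclusion criteria".

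The Data analysis section states the primary test: "The proportion of residents whose SDM documentation on needs satisfaction has been fulfilled, will be analyzed using the Fischer's exact test". On baseline differences it says: "Descriptive statistics will be used to compare the experimental and control nursing home wards for socio‐demographic characteristics and baseline variables".

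**The concern.** When whole wards are randomised, randomisation protects the comparison of residents only if their selection does not depend on the arm. If residents are chosen after the arm is known, the two groups can differ at entry although the wards were allocated fairly.

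Two routes are plausible here. Whoever selects may favour residents who can take part in a conversation, or who have engaged families, where an SDM interview will follow. Family willingness may also filter differently without any deliberate choice. In the experimental wards, agreeing to participate means joining a three-way interview, and the article describes no such interview for control families.

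Communication ability and family engagement could plausibly influence whether preferences are known and documented, the resident's own quality-of-life answers, and the family's sense of competence. At stake is the between-arm signal of potential effectiveness, which the article says will help to test the feasibility of a full trial.

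**Working it through.** **Stated numbers.** 2 experimental wards × 20 = 40 residents, and 2 countries × 8 = 16 professionals. Both agree with "the entire experimental group is composed by a total of 40 dementia residents, 40 family carers and about 16 healthcare professionals". With the control wards, 4 × 20 = 80 residents. The article gives no power calculation to reproduce.

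**Order of steps.** Three statements in Subjects and settings bear on it:

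1. Wards are randomised. No date is given.
2. Residents are included in wards that are already named by arm.
3. Control wards, named as such, are asked to supply matching numbers.

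Together they suggest that allocation comes before selection. No sentence gives the sequence outright, and none points to the opposite order.

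**What the check can do.** It compares selected residents with the inclusion criteria, so it can remove an ineligible resident. All 40 residents in each arm could pass it and the arms could still differ in severity, communication or family engagement.

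**What the analysis can do.** No adjustment is stated for the primary test, and baseline variables are compared descriptively. Table 1 includes demographics, CANE needs, Katz ADL and DQoL, but no measure of cognition or dementia severity. Strengths and limitations says that cultural differences and the family caregiver's presence at the interview will be taken into account. Neither addresses selection by arm.

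**Illustration 1: how a shift could arise (all inputs assumed).** Let the outcome probability be a in communicative residents and b in the others. Let the communicative share be f_E in the experimental arm and f_C in the control arm. With no intervention effect, the spurious difference is (f_E − f_C) × (a − b).

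- With a = 0.6, b = 0.3, f_E = 0.8 and f_C = 0.5, the experimental arm has 0.8 × 0.6 + 0.2 × 0.3 = 0.54. The control arm has 0.5 × 0.6 + 0.5 × 0.3 = 0.45. The difference is 9 points.
- With a = 0.6 and b = 0.2, the result depends on the assumed shares:

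| f_E | f_C | Experimental | Control | Difference |
|---|---|---|---|---|
| 0.6 | 0.5 | 0.44 | 0.40 | 4 points |
| 0.7 | 0.5 | 0.48 | 0.40 | 8 points |
| 0.8 | 0.4 | 0.52 | 0.36 | 16 points |
| 0.9 | 0.4 | 0.56 | 0.36 | 20 points |

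**Illustration 2: effect on the primary test (all inputs assumed except 40 per arm).** This is an exact enumeration of the two-sided Fisher test at an assumed alpha of 0.05, with 40 against 40 residents treated as independent and no intervention effect. Control proportions are 0.2, 0.3 and 0.5.

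| Shift from selection alone | Rejection rate, range over control proportions |
|---|---|
| 0 points | 2.8–3.3% |
| 5 points | 4.6–5.2% |
| 10 points | 10.5–12.3% |
| 15 points | 21.2–24.5% |
| 20 points | 36.8–40.8% |

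The rates show only how sensitive the test is to a given shift. They do not show that one will occur.

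**The case against.** The strongest reply is that the order of steps is read from labels. Calling wards experimental and control may simply be how an author describes a two-arm design. The article does not name the person who selects, and details of screening, sampling frame and timing of consent are commonly left to a full protocol. This stands as a limit on certainty, so the point has to be put conditionally. It does not remove the point, because the article does describe the selection step and its check, and that check does not address the risk.

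A reader might infer that the staff who will run the interviews pick residents with the arm known. The article does not say so. A reader might also infer that every comparison in the study is biased. That goes too far: within-group change is not an arm contrast, the process measures and focus groups are not presented as arm contrasts, and job satisfaction is measured on professionals. Feasibility and acceptability are less exposed.

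Other features help a little. Both arms share the inclusion criteria, numbers and tools, and the two Italian homes are to be similar in size, staffing and care. Baseline measures are taken in both arms and could reveal part of an imbalance. None of these prevents eligible residents from being chosen differently by arm.

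Two further points stand. The primary outcome is found by a researcher's review of plans that staff write, so its dependence on a resident's communication is plausible but assumed. Room for selection also depends on how many eligible pairs each ward has beyond 20, which the article does not give. A ward with only 20 would leave little room.

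**Conclusion.** The concern holds in a limited form. As Subjects and settings reads, residents appear to be selected within wards whose arm is known, and the later eligibility check cannot detect or prevent selection that differs by arm. The between-arm comparisons of resident and family outcomes are at risk, including the primary proportion.

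This rests on an inferred order of steps and on wards having more eligible pairs than they need. The size and direction of any bias cannot be derived from the document. The 54% against 45% example and the rejection rates are illustrations under assumed inputs, not estimates. The feasibility label lowers the stakes but does not remove them, since the article also claims to assess potential effectiveness and tests a primary outcome. The change is worth making because it is cheap.

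**What to change.** In both wards of each country, list all eligible resident-family pairs. Take 20 at random or consecutively, and obtain consent before the ward allocation is drawn or disclosed. Take baseline measures before disclosure too, where practicable. State this order in the protocol, and say who selects.

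If allocation is already known, let the researcher who now checks the choices draw the 20 from the full eligible list instead. In either case, report the numbers eligible, approached and refused by ward. These are useful feasibility data in their own right.

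The cost is the work of compiling the list and a short delay before training. The delay is longer if baseline is completed first, because CANE is collected from three informants for each of about 80 residents. That is why baseline before disclosure is asked for only where practicable. No extra residents are needed.

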### Intervention

As shown in Figure 1, the present project is a multifaceted intervention consisting of four phases to implement an SDM framework in (long‐term) care planning, to obtain a constantly developing plan that focuses not only on the medical, physical, psychosocial and spiritual needs of the residents, but that considers and documents their preferences and the actions taken by caregivers to meet them.

**Figure 1 nop242-fig-0001:**
[figure not shown]
Graphical representation of the intervention,

#### a) Pre‐intervention assessment − Dementia residents' (un)met needs assessment

At baseline (Table 1), a trained researcher will administer an adapted version of the Camberwell Assessment of Needs in the Elderly (CANE) (Orrell & Hancock 2004, Orrell *et al*. 2007) to the dementia residents and to the formal and informal caregivers. The CANE is a comprehensive, person‐centred needs assessment tool that has been designed for use with older people: the instrument is based on the principle that identifying a need means identifying a problem plus an appropriate intervention which will help or meet the need. It assesses the older person's needs from various perspectives: to reach this goal, CANE is to be administered not only to the older person but also to a key staff member and to an informal caregiver. The CANE has shown a good validity and reliability (Reynolds *et al*. 2000). In this study, only those items of the Dutch (Van der Roest *et al*. 2008) and Italian (Chattat & Celeste 2008) version of the CANE will be used to assess specific psychosocial needs of dementia persons who live in LTC settings. This was decided after discussion with the involved professionals as they declined the use of the full CANE questionnaire because of its length and relevance for nursing homes. They considered the need to manage behavioural problems, the need for tailored activities and the emotional and social needs as most important for residents with dementia in LTC settings (Cadieux *et al*. 2013). Starting from these data, we tried to improve the study protocol by discussing it with professionals to be involved. The items' relevance for nursing homes was related to a model for nursing home care, the Eden Alternative that aims to provide a person‐centered care environment for older residents (Brownie & Nancarrow 2013). On the basis of its principles, we have selected the CANE items that cover the following psychosocial issues: self‐care; daytime activities; psychological distress; information; behaviour; company and intimate relationship. The outcome of the selected CANE items will be a summary of met and unmet needs. The trained researcher who administers the CANE will share and discuss the information gained with the LTC professionals involved in the study before they will conduct the SDM interviews with the dementia resident and his family caregiver, so that they can use this information as a guidance for the interview. This will facilitate the selection and prioritization of their needs and the identification of possible interventions to meet them.

**Table 1 nop242-tbl-0001:** Overview of outcomes measure

Variable	Instrument	Time of assessment	
		B	F1
